### Intervention group

An alcohol therapist will attend the departments on days randomly drawn by a computer. He/she will go through the collected questionnaires, and patients with a score of eight or more in the Alcohol Use Disorders Identification Test will be contacted. The therapist will inform the patients that he/she comes from the outpatient alcohol treatment clinic. The patient will be informed about the study and if he/she consents, the alcohol therapist performs the Relay Intervention including a brief intervention. The therapist will interact with the patient in a non-confrontational and patient-centred manner by using the technique from motivational interviewing [32]. For patients with a score of 16+ in the Alcohol Use Disorders Identification Test, the significance of continuing an outpatient aftercare treatment and suggestion of a contract and an appointment to the alcohol treatment clinic is discussed. The design of the attendance contract is inspired by Lash & Blosser [33], and contains options for attending the outpatient clinic. Finally, patients will be informed that they will most likely meet again; if the patient participates in the outpatient aftercare treatment and that they will receive two letters at two weeks intervals, offering a new appointment should they not meet in the outpatient clinic at the agreed time. The intervention is expected to last 20 min.

### Control group

Patients in this group will receive the usual procedures from the department’s staff.

### Baseline data

To reduce the risk of disturbing the work of the department staff, recruitment data will be limited to data from the Alcohol Use Disorders Identification Test along with few demographic data in the questionnaire.

### Follow-up data

Each Dane has a unique personal registration number [34]. By means of the Danish Civil Registration System, the patients will be followed through the Danish National Patient Registry [35], the Danish Registry of Causes of Death [36] and the Danish National Alcohol treatment Registry [37]. By obtaining data from these registers, we will be able to assess the impact of the interventions on each patient’s use of all possible health care services. Data from all registries will be collected 12 and 60 months after discharge from the departments.

### Objectives

Our primary hypothesis is that the Relay Model will be cost-effective; hence, more patients assigned to the Relay Model will reach the local outpatient clinics. Firstly, we expect that this will lead to a change in alcohol consumption, and further lead to significant reductions in utilization of healthcare services at 12 months follow-up compared to patients assigned with usual referral procedures. Secondly, we expect that significantly more patients assigned to the Relay Model will report for outpatient alcohol treatment when compared with patients assigned to the usual referral procedures. Finally, we expect cost reductions in other societal costs (labour supply, social costs, and traffic accident costs) as well and in public expenditure for income loss compensations at 12 months follow up for patients assigned to The Relay Model.

## Outcomes

### Primary outcome

Health care expenditures 12 months after discharge.

### Data and analysis

Health care expenditure will be measured according to the International Classification of Health Accounts [38], and almost all components can be extracted from the following population registries:The Danish National Patient Register [35]The Danish National Health Service Register [39]The Danish National Prescription Registry [40]The Danish Psychiatric Central Research Register [41]

Only ICHA-HC.3 components services of long-term nursing care will not be included in the above mentioned, neither are other national registers, but these will be collected at municipality levels (from Odense Municipal). Whether a particular health care expenditure is related to alcohol will require judgment, which will be undertaken by two clinical assessors who are blinded to patient allocation.

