## Background

Compared to other countries the Danish population has a large intake of alcohol per capita, and almost all adolescents and adults in Denmark drink alcohol [1]. It is estimated that approximately 20 % of the adult population are heavy drinkers consuming >14/21 drinks/week (women/men), 14 % have a harmful alcohol use, and 3 % are dependent drinkers [2]. In Denmark the vast majority of services offered to patients suffering from alcohol use disorders are publicly funded and provided by a highly diverse group of about 60 specialized outpatient clinics, treating nearly 16,000 patients per year [3]. This is a small fraction of the estimated 140,000 alcohol dependent Danes [2], who needs specialized alcohol treatment.

Alcohol use disorders are associated with considerable societal costs and welfare losses to the Danish population. Annual societal costs include excess health care consumption, income loss compensations, children and youth intervention costs [3], production loss due to alcohol related short and long-term inability to work and premature death [4], and costs of alcohol related criminal activity and traffic accidents [5].

Carefully designed prevention and treatment interventions for alcohol use disorders can, if put into scale, help thousands of Danes and in addition generate economic benefits in terms of savings in the costs to society, listed above. Even if specialized treatment delivery itself is costly, it may generate sufficient savings to become cost-effective and perhaps even net-cost-saving [6]. A first approach may be to identify and recruit patients from general hospitals.

Alcohol use disorders are responsible for considerable physical morbidity and accidents, and many patients with alcohol problems are admitted to the general hospitals [7, 8]. In a systematic review of hospital screening studies the proportion of inpatients with alcohol use disorders was found to range between 16 and 26 % [9]. The prevalence is influenced by many factors: e.g. patient population, definitions, and assessment methods. The prevalence of dependence, determined by a diagnostic instrument, among patients in general hospitals is very high [10].

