### Analysis

The primary outcome, health care expenditures, will be calculated in two parts. First, a chi-square test will be used to do a crude comparison of the attendance rates of the two groups (intervention and control). Second, health care costs differences will be measured and tested using difference-in-difference analysis. The secondary outcome, societal costs, will also consist of two parts. First, the effect; a marker of reduced alcohol consumption after 12 months (i.e. alcohol related health care contacts), will be assessed in a difference-in-difference analysis. Second, the societal costs will be analysed like health care costs. Cost data are non-Gaussian and non-linear statistical models and bootstrapping techniques will be used in the statistical analyses.

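### The listed cost sources name neither the alcohol clinics nor delivery of the Relay Model, and the drinking marker does not exclude clinic visits, so both sides of the cost-effectiveness comparison are open to bias

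*Protocol article*

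**What the plan says.** The primary outcome is "Health care expenditures 12 months after discharge". For its measurement, the Data and analysis section states that "almost all components can be extracted from the following population registries" and lists the National Patient Register, the National Health Service Register, the National Prescription Registry and the Psychiatric Central Research Register. It then names one gap: "Only ICHA-HC.3 components services of long-term nursing care will not be included in the above mentioned". Nursing care is to be collected from the municipality.

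The Follow-up data section gives a different list. Besides the National Patient Registry it names "the Danish Registry of Causes of Death [36] and the Danish National Alcohol treatment Registry [37"], and says that these registers will show each patient's "use of all possible health care services", with data collected at 12 and 60 months.

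The Background places specialised alcohol treatment in about 60 publicly funded outpatient clinics and accepts that it costs money ("Even if specialized treatment delivery itself is costly"). The Objectives section expects more Relay patients to reach those clinics. The Intervention group section describes a therapist contact of about 20 minutes on the ward, an attendance contract and up to two letters after a missed appointment.

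In the Analysis section, the effect is "a marker of reduced alcohol consumption after 12 months (i.e. alcohol related health care contacts"), tested by difference-in-difference. Whether an expenditure is related to alcohol is left to two blinded assessors (Data and analysis). No rule is given for visits to the alcohol clinics.

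**The concern.** Two separate weaknesses follow from the wording.

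**Cost.** Four registers with one declared exception is a statement of scope, not silence. Read as it stands, it gives no cost source for clinic treatment or for Relay delivery. Both are resources that the model adds in one arm. Leaving them out would overstate any saving, and a claim of cost neutrality is especially sensitive to omitting the intervention's own cost. Difference-in-difference does not help, because the omitted cost arises after allocation and differs between the arms.

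**Effect.** Fewer alcohol-related contacts are to stand for less drinking. A visit to an alcohol clinic is related to alcohol on any ordinary judgment. If such visits are counted, a successful referral raises the marker and counts against the model. The assessors' blinding to allocation does not prevent this.

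**Working it through.** **1. The source lists side by side**

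| Source | Cost list (Data and analysis) | Follow-up data |
|---|---|---|
| National Patient Register | yes | yes |
| National Health Service Register | yes | no |
| National Prescription Registry | yes | no |
| Psychiatric Central Research Register | yes | no |
| Causes of Death | no | yes |
| National Alcohol treatment Registry | no | yes |
| Municipal nursing care data | yes, as the one exception | no |
| Relay contact, contract, letters | no | no |

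The lists share only the patient register. The follow-up list names the treatment registry in addition to the patient register, which suggests that the authors do not expect the patient register alone to show clinic treatment. That is an inference, because the document does not say what each register covers.

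**2. The plan's own figure**

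Inputs from the Power calculation section: mean excess cost 88,067 DKK, reduction 26 %, standard deviation 144,967 DKK, power 80 %, about 500 per group.

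- Target difference: 0.26 × 88,067 = 22,897 DKK, as stated.
- Patients per group: n = 2 × (z_α + z_β)² × (SD / difference)², with (144,967 / 22,897)² = 40.08.
- One-sided 5 %: 2 × (1.645 + 0.842)² × 40.08 gives 496, which reproduces about 500.
- Two-sided 5 %: 2 × (1.960 + 0.842)² × 40.08 gives 630, which does not.

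Alpha and sidedness are not stated. The one-sided 5 % level is used below only because it reproduces the plan's figure. The concern does not depend on it.

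**3. How large the omitted cost could be**

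Omitted cost per Relay patient = R + d × T, where R is the cost of Relay delivery, d the extra share of patients who attend because of Relay, and T the treatment cost per attender. The document gives none of these, so the ranges are assumptions: R from 500 to 1,000 DKK, d from 0.10 to 0.50, T from 5,000 to 30,000 DKK.

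- Low end: 500 + 0.10 × 5,000 = 1,000 DKK, and 1,000 / 22,897 = 4 %.
- Middle example: 500 + 0.20 × 20,000 = 4,500 DKK, and 4,500 / 22,897 = 20 %.
- High end: 1,000 + 0.50 × 30,000 = 16,000 DKK, and 16,000 / 22,897 = 70 %.

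If the gross saving were 22,897 DKK, the net difference would be 21,897, 18,397 or 6,897 DKK. With 500 per group, power for that net difference would be 77 %, 64 % or 19 %, against 80 % for the gross one.

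The contract and clinic appointment are discussed only with patients scoring 16 or more, while contact starts at a score of 8. If patients scoring 8 to 15 are part of the 500, d across the arm is diluted, which favours the lower end of the range.

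**4. The marker**

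No arithmetic is possible. If the marker is built from the cost list and those registers miss the clinics, clinic visits do not enter it. If it is built from the follow-up list, which includes "the Danish National Alcohol treatment Registry [37"], they do enter it unless excluded, and the Analysis section states no exclusion.

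**The case against.** The strongest reply is that treatment data are already planned. The Follow-up data section names the treatment registry and claims full coverage of service use at the primary horizon, and no sentence removes clinic treatment from cost. Nor does the document say that the four registers miss the clinics. This stands: the omission is likely on the wording but not proven.

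Second, the two halves rest on different lists. If the follow-up list governs throughout, the cost problem weakens. If the cost list governs throughout and misses the clinics, the marker problem disappears. A reader might infer that the result is distorted on both sides at once. The document does not support that as fact. It leaves room for both, since one list serves costs and the other follow-up, but it commits to neither.

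Third, unit costing of a 20-minute contact and two letters may sit in the full protocol or analysis plan, and the ward contact takes place before discharge whereas the primary outcome counts expenditure after it. This too stands, so the Relay delivery item is the weaker part of the cost point.

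Fourth, the marker belongs to a secondary outcome, and uptake is also compared directly by chi-square, so higher attendance would be visible. That helps a careful reader interpret the marker but does not correct it.

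Finally, it is tempting to treat 22,897 DKK as the saving per extra attender and say that treatment at 5,000, 10,000 or 20,000 DKK cancels 22 %, 44 % or 87 % of it. The Power calculation section uses that figure as the average difference to be detected between groups, and in total additional expenses rather than health care expenditure alone. Those percentages should not be used.

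**Conclusion.** The point holds as a risk that the current wording creates, not as a demonstrated bias.

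- **Cost:** if the four registers do not capture the alcohol clinics, the primary cost difference is biased towards Relay. Its size is unknown. Under the assumed inputs it lies between 4 % and 70 % of the target difference per Relay patient, so it could be trivial or could remove most of the saving.
- **Effect:** if the source used for the marker captures clinic visits, the effect is biased against Relay, by an amount that cannot be computed.

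The two biases act on different quantities, so they cannot be assumed to cancel. This is more than missing detail: the cost section declares what lies outside its sources, and the declaration does not match the follow-up section. It should be fixed before analysis, but it does not by itself invalidate the trial.

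**What to change.** 1. Reconcile the register lists in Data and analysis and in Follow-up data, and state which sources feed the primary cost outcome and which feed the marker.
2. Add outpatient alcohol treatment to the cost comparison in both arms, as contacts from the treatment registry multiplied by a unit cost.
3. Add Relay delivery (therapist time, contract, letters) for the intervention arm. Say how the part that falls before discharge enters the comparison.
4. Report the cost difference with and without items 2 and 3.
5. Define the marker as alcohol-related health care contacts excluding contacts with the alcohol treatment clinics, and give the assessors that rule in writing.

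The price is a unit-cost table and a coding rule. The treatment registry is already planned, so no new patient data are needed. The downside is a cost result that may be less favourable to the model.

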### Secondary outcomes

The percentage of the target group who 30 days after discharge reports at the alcohol treatment clinics and other societal costs including value of alcohol related loss of production.

### Data

IDA National Registry (Integrated Database for Labour market Research), Public expenditures for alcohol related income compensations measured using the DREAM National Registry (Database of Welfare payments and Social benefits) and by PUOB Registry (Database for persons without ordinary occupation).

### Power calculation

In the absence of data from general hospitals, we use data for the power calculation stemming from the study by Parthasarathy et al., who found that outpatient treatment decreased the consumption of health services by 26 % [29]. Primary outcome is the socio-economic costs of alcohol-abuse patients. Based on information from the Danish Institute of Governmental Research we have an estimate of the average total additional expenses for alcohol abuse patients of 88,067 DKK. Treatment for alcohol dependence is expected to lower the additional costs by 26 %. Since the individual excess costs of patients is highly variable with a standard variation of 144,967 DKK, the coefficient of the variation is quite high. Therefore, the power calculation results in a total of about 500 patients in each of the two groups in order to be able to detect the average decrease in total additional expenses of 22,897 DKK, with 80 % probability.

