The incidence of patients with alcohol-related diseases is greatest in the departments receiving patients with the following conditions: falls, collapse, head injuries, assaults, gastrointestinal problems, unwell, neurological-psychiatric problems, cardiac symptoms and accidents [11, 12]. In Denmark such patients will typically be admitted to gastrointestinal (liver disease, oesophagitis, gastritis, pancreatitis), neurological (including seizures, head injure, stroke, peripheral neuropathy and vascular disease) and orthopaedic departments (falls, assault, accidents).

Many studies have examined brief interventions for patients in general hospitals [13–15], but it is not well established if alcohol dependent patients benefit from the interventions [16]. A more intensive and prolonged treatment delivered by specialists seems to be needed for the patient group suffering not only from problem drinking, but from alcohol dependence as well [17–20].

In studies on recovery from alcohol use disorders, health problems and hospital admission were among the most cited predictors of recovery [21]. Patients with alcohol use disorders admitted to general hospitals seem much more likely to be motivated for change than a comparable group of alcohol dependent patients in the community [22]. Individuals hospitalized with alcohol use disorders, even just assigned to control groups with no other intervention than assessment, seems significantly more often to remain non-problem drinkers or abstinent after discharge, compared with patients stemming from general practice [23]. In other words; health problems and hospital admission could open a window for changing alcohol consumption. Therefore, general hospitals seem to be in an outstanding position to detect and refer individuals with alcohol use disorders to specialized alcohol treatment.

Several studies have shown that between 36 and 54 % of hospitalized patients do not engage in psychosocial treatment after discharge, and between 20 and 90 % will subsequently relapse back to renewed alcohol abuse [24]. Therefore, barriers to engage in treatment for alcohol use disorders seem to exist. The low number of successful referral rates from inpatient to specialized alcohol treatment represents missed opportunities for patient improvement and cost savings [25].

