Lash et al. found that having a therapist complete an aftercare group therapy attendance contract with patients at the completion of inpatient treatment, resulted in significant greater aftercare adherence [26]. In another study, Lash et al. investigated whether a treatment contract drafted by the outpatient therapist at discharge, followed by feedback and reminders in the form of telephone calls and letters, increased the turnout for outpatient group treatment, when compared to a control group who were offered only a treatment contract, drafted by the outpatient therapist. The study showed that significantly more patients in the intervention group began outpatient treatment, and after 12 months significantly more patients in this group were still abstinent/drug-free [27].

The purpose of a referral model is to increase the proportion of patients with alcohol use disorders who start specialized alcohol treatment after being discharged from the hospital. In order to be implemented in the health care system, the model must show an impact on both outcomes for patients and on the overall cost to the health care system. Hence, studies on referral models need to include analyses of cost-effectiveness [28]. In the alcohol treatment field, only few publications describe the cost-effectiveness of treatment alternatives. In a study of an outpatient abuse program in the United States, patients were followed 18 months before and 18 months after starting treatment. After treatment was initiated, a decrease in consumption of health services by 26 % was found [29]. Holder also found a decrease in the use of health services after initiation of treatment [30].

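### The power calculation uses the full 26 % effect of receiving treatment as the between-arm difference, although the trial randomises an offer of referral

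*Protocol article*

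**What the plan says.** The Power calculation section of the protocol article takes its effect from a cited study, "who found that outpatient treatment decreased the consumption of health services by 26" per cent. It starts from "average total additional expenses for alcohol abuse patients of 88,067 DKK", gives a standard deviation of 144,967 DKK, and states that "Treatment for alcohol dependence is expected to lower the additional costs by 26" per cent. It concludes that about 500 patients per group are enough to "detect the average decrease in total additional expenses of 22,897 DKK, with 80 % probability". Alpha and sidedness are not given, nor is an attendance rate in either arm.

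Other sections describe what is randomised and what is known about uptake:

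- **Allocation concealment** and **Intervention group**: the computer draws the days on which an alcohol therapist visits the ward. Patients scoring 8 or more are contacted, and those who consent receive a contact of about 20 minutes that includes a brief intervention. The contract and clinic appointment belong to a subgroup: "For patients with a score of 16+ in the Alcohol Use Disorders Identification Test, the significance of continuing an outpatient aftercare treatment" is discussed together with them.
- **Abstract** and **Control group**: controls are referred by usual procedures; treatment is not withheld.
- **Background**: in cited studies, "between 36 and 54 % of hospitalized patients do not engage in psychosocial treatment after discharge". The source of the 26 % is described as one in which "patients were followed 18 months before and 18 months after starting treatment".
- **Secondary outcomes**: reporting at the treatment clinics within 30 days is itself an outcome.

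**The concern.** The 26 % describes what happened after people started treatment. The two arms differ in whether a therapist came to offer a route into treatment. Using the first quantity as the second assumes 100 % treated in one arm and 0 % in the other. A trial that sets out to learn whether attendance differs cannot take that difference as complete when it computes power.

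The primary outcome is at stake. If power is well below 80 %, a non-significant 12-month cost comparison is a likely result even where treatment works exactly as assumed. The Abstract expects to show whether the model is cost-neutral or cost-effective, so such a result could easily be misread as cost-neutrality or as absence of effect.

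**Working it through.** **Inputs** (all from Power calculation unless noted): mean 88,067 DKK; relative reduction 26 %; SD 144,967 DKK; 500 per group; power 80 %. Engagement of 46–64 % is the complement of the 36–54 % in Background. Attendance differences of 30 and 20 points are my assumptions.

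**Step 1: the difference powered for.** 0.26 x 88,067 = 22,897 DKK, exactly the stated figure. No reduction for uptake has been applied.

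**Step 2: reproducing 500 per group** (normal approximation, n = (z_alpha + z_beta)² x (SD₁² + SD₂²) / difference²):

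- One-sided 5 %, equal SDs: (1.645 + 0.842)² x 2 x 144,967² / 22,897² = 496 per group; power at 500 is 80.3 %. Reproduces.
- Two-sided 5 %, SD proportional to the mean (treated SD 0.74 x 144,967 = 107,276): 487 per group; power at 500 is 81.0 %. Reproduces.
- Two-sided 5 %, equal SDs: 630 per group; power at 500 is 70.4 %. Does not reproduce.

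The first two conventions give about 500, and only with the undiluted 22,897 DKK. I show the third because it is a common default, but its shortfall from 80 % to 70 % has nothing to do with dilution.

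**Step 3: dilution.** Let f be attendance in the intervention arm minus attendance in control. If the cost effect acts through attendance, the expected difference is f x 22,897 DKK. Power = Φ(difference / SE − z_alpha), where SE = 144,967 x √(2/500) = 9,169 DKK with equal SDs. With SD proportional to the mean, the intervention SD is 144,967 x (1 − 0.26f).

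For f = 0.64 the difference is 14,654 DKK. One-sided with equal SDs: 14,654 / 9,169 = 1.598, and Φ(1.598 − 1.645) = 48 %.

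| Attendance difference | Difference (DKK) | One-sided 5 %, equal SDs | Two-sided 5 %, SD proportional to mean | Two-sided 5 %, equal SDs |
|---|---|---|---|---|
| 100 points (implied) | 22,897 | 80 % | 81 % | 70 % |
| 64 points (best cited engagement, no control attends) | 14,654 | 48 % | 41 % | 36 % |
| 46 points (worst cited engagement, no control attends) | 10,533 | 31 % | 23 % | 21 % |
| 30 points (assumed) | 6,869 | 19 % | 12 % | 11 % |
| 20 points (assumed) | 4,579 | 13 % | 7 % | 7 % |

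**Step 4: what 80 % would take.** With equal SDs, a 64-point difference needs 1,211 per group (one-sided) or 1,537 (two-sided); 46 points needs 2,343 or 2,974. At 500 per group, power stays within two points of 80 % in the two reproducing conventions only if the attendance difference is about 97 points or more (78 % in both at 97 points).

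**The case against.** **The dilution formula is a model.** Every consenting intervention patient scoring 8+ receives a brief intervention, and Methods says scores of 8–15 benefit from one. Costs may therefore also fall in patients who never attend, which would soften the dilution. This stands as a qualification. The power section, however, claims no such effect and takes its reduction from treatment, and Background calls the benefit of brief interventions in dependent patients not well established.

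**The attendance rates are not the trial's own.** The 36–54 % comes from cited studies of hospitalised patients, and pairing it with zero control attendance is my construction. This also stands: the exact power is unknown. For a given engagement rate, though, zero control attendance is the most favourable choice.

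**The planned analysis and outcome differ from the calculation.** A difference-in-difference analysis changes precision, in a direction set by a pre-post correlation that is not given. With a simple change score and equal variances, the SD is multiplied by √(2(1 − r)). At an assumed r = 0.7 the factor is 0.77, and power at 64 points becomes 66 % one-sided or 54 % two-sided; below r = 0.5 it falls. The SD also refers to total additional expenses, whereas the primary outcome is health care expenditures, so no fixed confidence-interval width for that outcome can be derived from it.

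**Stronger readings.** A reader might infer that the primary comparison is nearly certain to be null. The documents do not support that: at the best cited engagement power is 36–48 %, and the very low figures belong to assumed attendance differences. A reader might also infer that part of the 26 % would occur in controls, because Background says "After treatment was initiated, a decrease in consumption of health services by 26 % was found" and mentions no comparison group. That brief summary does not show whether the figure was net of one.

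**Conclusion.** The point holds. The stated 80 % belongs to a comparison of everyone treated with no one treated, which is not the comparison this trial makes. If the cost effect acts mainly through attendance, power at 500 per group is below 50 % even at the most favourable cited engagement: 48 % or 41 % in the conventions that reproduce the plan's figure, and 36 % at two-sided 5 % with equal SDs. At the lower cited engagement it is 31 %, 23 % or 21 %.

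These sizes rest on the stated SD, on no cost effect of the brief intervention in non-attenders, and on no gain or loss of precision from the difference-in-difference analysis. The dilution itself rests on less: it follows unless attendance is close to complete in one arm and close to absent in the other, or effects outside attendance make up the gap.

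**What to change.** In Power calculation, replace the 80 % claim with power for the intention-to-treat effect, defined as 26 % times an explicit attendance difference and tabulated over a range. State alpha, sidedness and the SD assumption with it.

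State that a non-significant 12-month cost result will be interpreted through its confidence interval and will not be taken as evidence of cost-neutrality or of no effect.

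Report attendance and cost by AUDIT 8–15 and 16+ in both arms, since the contract and appointment are offered only to the upper group.

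An instrumental-variable estimate with allocated day as instrument for attendance is not a suitable remedy: the bedside brief intervention is a direct path from allocation to cost. Nor should the section claim that 500 per group powers the attendance comparison if that comparison is confined to scores of 16+, because that subgroup is smaller than the full arm.

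The cost is a rewritten paragraph, a lower stated power and a little extra analysis of data already planned. No change to recruitment is required.

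### The power calculation uses the full 26 % effect of receiving treatment as the difference between two referral arms, so 80 % power needs an attendance gain of nearly 100 points unless the ward brief intervention makes up the shortfall

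*Protocol article*

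**What the plan says.** The Power calculation section of the protocol article takes its effect from a study of outpatient treatment, "who found that outpatient treatment decreased the consumption of health services by 26" %. It then states that "Treatment for alcohol dependence is expected to lower the additional costs by 26" %. The cost base is "average total additional expenses for alcohol abuse patients of 88,067 DKK", described as "highly variable with a standard variation of 144,967 DKK". The result is about 500 patients per group, to "detect the average decrease in total additional expenses of 22,897 DKK" with 80 % probability. Alpha and sidedness are not given, and no allowance is made for attendance.

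Other sections describe what is randomised. According to the Abstract, controls are referred to treatment in the usual way. The Objectives expect savings because "more patients assigned to the Relay Model will reach the local outpatient clinics". Under Intervention group, Relay patients scoring 8 or more receive a brief intervention on the ward. The attendance contract and clinic appointment are discussed with those scoring 16 or more, and letters are planned for patients who miss the appointment. Clinic attendance at 30 days is a secondary outcome. The Background reports that 36 to 54 % "of hospitalized patients do not engage in psychosocial treatment after discharge".

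**The concern.** The 26 % describes what happens to costs when a patient receives outpatient treatment. The calculation uses it, undiluted, as the average difference between everyone randomised to Relay and everyone randomised to usual referral. In effect every Relay patient is credited with the full treatment saving and no control with any of it. The protocol does not describe the trial that way: it expects more attendance, plans for missed appointments and leaves controls free to attend.

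At stake is the interpretation of the primary outcome, health care expenditures at 12 months. The Abstract's Discussion expects evidence that the model is cost-neutral or cost-effective. If the real power is well below 80 %, Relay could raise attendance, and treatment could save the full 26 % in those who attend, while the whole-arm comparison stays non-significant. A reader who trusts the stated 80 % could take that result as showing cost-neutrality.

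**Working it through.** **Inputs from the Power calculation section:** mean additional cost 88,067 DKK; SD 144,967 DKK; reduction 26 %; 500 per arm; power 80 %. **Assumed:** alpha 5 %, one-sided and two-sided both shown; attendance gain g (Relay attendance minus control attendance), varied because the protocol gives no rates by arm.

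**1. Where 22,897 DKK comes from.** 0.26 × 88,067 = 22,897. This is exactly the full treatment effect, with no dilution.

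**2. Reproducing about 500 per arm.** n = 2 × [144,967 × (z_alpha + 0.842) / 22,897]².
- One-sided 5 % (z = 1.645): 496 per arm, which matches.
- Two-sided 5 % (z = 1.960): 630 per arm, which does not match under a constant SD.
- Two-sided 5 % with the Relay SD falling in proportion to the mean (0.74 × 144,967): 487 per arm, which is also close to 500.

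**3. Slack in the design.** SE = 144,967 × √(2/500) = 9,169 DKK. The difference detectable with 80 % power is (1.645 + 0.842) × SE, about 22,800 DKK one-sided, or (1.960 + 0.842) × SE, about 25,700 DKK two-sided. The one-sided value before rounding, 22,797 DKK, is 99.6 % of 22,897 DKK, so almost the whole treatment effect must appear as the arm difference.

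**4. Allowing for attendance.** If the cost effect runs only through attendance, the expected arm difference is g × 22,897 DKK and power is Φ(g × 22,897 / 9,169 − z).

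| Attendance gain | Expected difference (DKK) | One-sided 5 % | Two-sided 5 % |
|---|---|---|---|
| 100 points | 22,897 | 80 % | 70 % |
| 54 points | 12,364 | 38 % | 27 % |
| 30 points | 6,869 | 19 % | 11 % |
| 20 points | 4,579 | 13 % | 7 % |

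The 54-point row is the largest gain possible if 46 % of controls attended, 46 % being the complement of the Background's 54 % non-engagement. It is an illustration and not a forecast. The 30- and 20-point rows are pure assumptions.

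**5. Sensitivity to the SD.** If the SD falls with the mean, two-sided power is 81 % at 100 points, about 30 % at 54 and about 12 % at 30.

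**6. Sensitivity to the planned analysis.** A difference-in-difference on change scores has SD 144,967 × √(2(1 − ρ)), where ρ is the pre/post cost correlation (same SD assumed before and after). At ρ = 0.5 nothing is gained. For a 50-point gain at two-sided 5 %, power is 24 % at ρ = 0.5, 36 % at 0.7, 51 % at 0.8 and 80 % at 0.9.

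**The case against.** The arithmetic reproduces: about 500 per arm does detect 22,897 DKK with 80 % power at one-sided 5 %. What is in dispute is whether that difference fits the randomised contrast. This is fair, and the point is about the effect-size assumption, not a slip in calculation.

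A reader might infer that the arms differ only in the share who attend, so that 80 % power holds strictly at 100 % versus 0 %. The documents do not support that. Relay patients scoring 8 or more also receive a brief intervention, and the Methods section says that patients in the 8–15 range benefit from one. The Background's doubt about brief interventions concerns dependent patients only. A direct effect on cost is therefore possible. The Power calculation section, however, credits no effect to it and attributes the 26 % to treatment.

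A reader might also infer that the Background figures fix attendance in the arms, or that they make a null cost result likely. They do neither. The 36–54 % comes from several cited studies whose setting and referral method are not described. The comparison of nearly 16,000 treated patients with 140,000 dependent Danes is a national annual ratio, and the trial excludes people treated in the previous 6 months. These figures show that complete attendance in one arm and none in the other is implausible, but not how large the gain will be.

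Finally, the power table is a plain two-sample test on total additional expenses. The primary outcome is health care expenditures, and the Analysis section plans difference-in-difference with non-linear models and bootstrapping. The table is therefore illustrative. The planned analysis could recover some power, but for a 50-point gain it reaches 80 % only if pre- and post-discharge costs correlate at about 0.9, and the Power calculation section claims no such gain.

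**Conclusion.** The concern holds in this form. The Power calculation section uses the effect of receiving treatment, undiluted, as the difference between two referral strategies. On the protocol's own pathway the expected difference is smaller, roughly the attendance gain times 22,897 DKK. The stated 80 % power then needs a gain of nearly 100 points, unless a direct effect of the brief intervention fills the gap. For illustration, power falls to 38 % one-sided or 27 % two-sided at a 54-point gain, and to 19 % or 11 % at 30 points.

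These figures assume a 5 % alpha, the section's constant SD, a two-sample z-test, no direct effect of the brief intervention and a 26 % saving that is correct for those treated. The conclusion that 80 % is overstated does not depend on any one row of the table. It needs only a gain clearly below 100 points, no compensating direct effect and no very high pre/post cost correlation.

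**What to change.** In the Power calculation section:

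- State alpha and sidedness.
- State the assumed attendance in each arm and any direct cost effect assumed for the brief intervention, and derive the expected arm difference from them.
- Restate power at 500 per arm over a range of attendance gains, including 20, 30 and 54 points. If credit is taken for difference-in-difference, state the assumed pre/post correlation.
- Alternatively, replace the 80 % claim with the whole-arm difference detectable with 80 % power: about 22,800 DKK one-sided or 25,700 DKK two-sided under a constant SD.

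Add that a non-significant cost difference will be interpreted from its confidence interval and not read as evidence of cost-neutrality. A blanket statement that any such result is inconclusive would go too far.

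A complier-average analysis, with the randomised day as instrument for attendance, is not needed for this correction. It assumes that the day affects cost only through attendance, which the brief intervention may violate. If included, it should be exploratory and carry that caveat.

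The cost is a rewritten section, with no extra patients or data. The downside is that the stated power becomes much less favourable.
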